### Sample size

This study is designed as a feasibility and acceptability study to inform a future, large-scale trial. Consequently, a formal power calculation is not required [7, 40]. The number of eligible households to be approached was selected as a means to facilitate estimation of recruitment and active participation rates. The number of households invited to participate in the intervention periods was guided by the need to ensure that equal numbers of households receive each of the four bottles sizes at each intervention period (i.e. the need to recruit a multiple of four households). The specific sample sizes were selected predominantly based on available resources (i.e. staff and funding) and our previous experiences of reducing key uncertainties in feasibility studies prior to finalising designs for randomised controlled evaluations of complex behavioural interventions.

### Qualitative component

Household representatives will be interviewed at the end of the study in order to assess acceptability of the intervention and of the study procedures, including the removal of existing drinks. The interviews will also be used to explore whether participants were conscious of the study’s primary aim and if so, whether they thought this knowledge influenced their household’s consumption of the cola. Interviews will be semi-structured and last approximately 1 h. They will be recorded and sent for external transcription. Transcripts of the interviews will be anonymised.

### Data analysis

The main analysis of this study will include descriptive statistics of feasibility and acceptability outcomes, including recruitment and attrition rates. We will also calculate the average change from baseline in SSB consumption during each intervention period to estimate possible effect sizes from which to power the main trial.

Analysis of the anonymised data gathered through the semi-structured interviews will be conducted following the principles of the Framework method [41].

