### Aim and objectives

The aim of the current study is to assess the feasibility and acceptability of conducting a randomised controlled trial of the impact of bottle size on consumption of cola in homes.

The specific objectives of the current study are to describe and assess the following:i.Feasibility of recruiting participants from eligible households into the trial, including estimating the recruitment rateii.Characteristics of recruited households, to judge the likelihood of recruiting a sample varied in potential effect modifiers (i.e. socioeconomic factors)iii.Bottle sizes that are most appropriate for use in the planned trialiv.Feasibility and practicalities associated with delivering the interventionv.Acceptability of the interventionvi.Awareness of the purpose of the interventionvii.Possible effect size, to inform sample size calculations for the planned trialviii.Feasibility and acceptability of the assessment proceduresix.Feasibility of collecting end - point datax.Loss-to-follow up rates

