### Design

We propose to use a crossover design in which general population households will each be exposed to four intervention conditions over time, randomised in their order of presentation. The unit of randomisation is the household. The four conditions will comprise receipt of a given quantity of a carbonated cola sugar-sweetened beverage (SSB), sub-divided into bottles of one of four different sizes (Fig. 1).

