**Fig. 1 Fig1:**
[figure not shown]
Flow of participants through the study

A within-subjects, crossover design is being used because of the variability between households, which will vary considerably by size, as well as their social and psychological characteristics. Being able to control for these differences makes a within-subjects crossover design preferable to a between-subjects design. It also maximises statistical power thereby increasing efficiency of research resource in terms of accruing the greatest reduction in uncertainty possible from participating households.

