All participating households will receive all interventions according to a pre-specified random order (see ‘Randomisation’ section for details). During the first intervention period, four households will receive cola in each of the intervention bottle sizes, subsequently crossing-over to the other conditions during the remaining three intervention periods, until all households have been exposed to all conditions. All intervention periods will be conducted during school term times, in order to avoid increased consumption during any specific period due to the increased presence of children in the homes. During the intervention periods, a researcher will visit participating households to deliver the total volume of the cola (Coca-Cola**®** or Pepsi Cola**®** depending on their preference) SSB for the forthcoming week. The researcher will remove any existing SSB products that are in the household, with financial compensation provided for any removals. At the end of each week, households will be requested to pay for the SSB drinks they consume at their usual purchasing rate. During the intervention periods, households will be requested to continue to keep all bottles whether the contents are consumed, partially consumed or not consumed. They will be told that the reason for this is to accurately estimate how much they need to pay for their drinks, based on the amount they consumed.

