### Randomisation

Randomisation will be restricted to ensure that (a) equal numbers of households receive each of the four bottles sizes at each intervention period (Table 1) and (b) each bottle size is equally likely to be preceded and followed by each other bottle size. These conditions are imposed to ensure that the order in which the interventions are presented is counterbalanced and that outcomes are not affected by potential order and carry-over effects. In a larger trial, such as the future one we are planning, we do not foresee the need for imposing such restrictions, as randomisation of a large number of households is expected to minimise the chance of imbalances in the order of the interventions.

**Table 1 Tab1:** Number of households allocated to each bottle size during each intervention period

	Bottle size			
	250 ml	500 ml	1000 ml	1500 ml
Intervention period 1	*n* = 4	*n* = 4	*n* = 4	*n* = 4
Intervention period 2	*n* = 4	*n* = 4	*n* = 4	*n* = 4
Intervention period 3	*n* = 4	*n* = 4	*n* = 4	*n* = 4
Intervention period 4	*n* = 4	*n* = 4	*n* = 4	*n* = 4

We will initially randomly select four sequences (out of 24 available sequences) dictating the order in which households receive each bottle size. These four sequences will then be used to determine the other 12 sequences needed to balance the initial allocations to ensure that the aforementioned conditions are met. Each household will be randomly allocated to one of these 16 sequences. In this manner, the order in which each household receives each bottle size will be pre-specified at the start of the study. The randomisations will be determined during the run-in period (see ‘Procedure’ section) by a statistician independent from the research team, with the assistance of computer software.

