### Procedure

Participation will comprise seven stages:Two-week recruitment and baseline assessment period (see ‘Baseline assessments’ section for details).One-week run-in period. Households will receive a range of differently sized bottled drinks to store in their homes to consume freely. This period functions to acquaint them with both the idea that a wide range of bottle sizes is available and that drinks will be delivered to them over the course of the study. More generally, it will build credibility of the study as a consumer research exercise. Study randomisation will be conducted during this period.First intervention period: 1 week in duration.Second intervention period: 1 week in duration.Third intervention period: 1 week in duration.Fourth intervention period: 1 week in duration.End of study and debriefing.

Stages 1–2 will be completed by any number of eligible households out of the 100 approached that agree to do so.

Stages 3–7 will be completed by 16 households, randomly selected from those completing stages 1–2, who also express a willingness to continue participation in the study. If only 16 households agree to continue their participation, all will be invited to complete these additional stages.

Each household will receive £150 worth of shopping vouchers at the end of the study for completion of all intervention periods and follow-up assessments. This amount was determined based on the national minimum wage rates per hour and the level of commitment and amount of time spent participating in the study (approximately 25 h during 5-week period). Households completing the run-in period but not invited to continue their participation, or not interested in continuing, will receive £30 worth of shopping vouchers.

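### Read by its own definition of intervention period, the stated effect-size summary contains no contrast between bottle sizes; read by bottle size, each change from baseline taken alone is mixed with study effects

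*Protocol article*

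**What the plan says.** The purpose of the planned trial is given under Aim and objectives: it is a "randomised controlled trial of the impact of bottle size on consumption of cola in homes". Objective vii asks this study for a possible effect size to inform that trial's sample size. Under Design, "households will each be exposed to four intervention conditions over time, randomised in their order of presentation". The text after Fig. 1 defends the crossover on the ground that households differ a great deal: "Being able to control for these differences makes a within-subjects crossover design preferable to a between-subjects design".

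The Data analysis section then names one effect-size summary: "We will also calculate the average change from baseline in SSB consumption during each intervention period to estimate possible effect sizes", for use in powering the main trial. The article describes no other effect-size summary.

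The term intervention period is fixed elsewhere. The Procedure section lists four numbered stages, beginning with "First intervention period: 1 week in duration". The Randomisation section requires that "equal numbers of households receive each of the four bottles sizes at each intervention period", and Table 1 sets periods 1 to 4 as rows against bottle sizes as columns, with n = 4 in all 16 cells. The Intervention section agrees for the first week: "During the first intervention period, four households will receive cola in each of the intervention bottle sizes". The number of households is set in the Procedure section: "Stages 3–7 will be completed by 16 households, randomly selected from those completing stages 1–2".

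**The concern.** Period and bottle size are separate factors in Table 1, and the allocation is deliberately balanced so that neither is confounded with the other. A summary by period averages over size. The same counterbalancing that protects the comparison of sizes therefore removes that comparison from the summary the plan names. An analyst who followed the sentence literally would obtain four weekly mean changes that show how consumption drifted over the study and how it differed from baseline. They would not show how it differed between a 250 ml and a 1500 ml bottle.

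Objective vii is at stake. The figure is meant to go into the sample size of the main trial, and a before-after change is not the quantity that trial will test. The point does not turn on detail that could be left to an analysis plan: the article names a specific summary and a specific use for it.

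**Working it through.** **Inputs.** 16 households, 4 periods and 4 sizes, with n = 4 per size in each period (Table 1). The document gives no effect size or SD, so the size effects below are assumptions chosen only to show the mechanism.

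**Reproducing Table 1.** A balanced 4 × 4 sequence square used four times gives 16 sequences. It yields 4 households per size in every period, and each ordered pair of sizes is adjacent 4 times. This matches Table 1 and both restrictions in the Randomisation section.

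**Reading 1: period means numbered week.** Take an additive model without carry-over for change from baseline in period j on size k: change = μ + π_j + τ_k. With 4 of 16 households on each size,

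mean for period j = μ + π_j + (τ_250 + τ_500 + τ_1000 + τ_1500)/4.

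The last term is the same in every period. Setting μ and π_j to 0:

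| Assumed effects, ml (250, 500, 1000, 1500) | Mean in each of periods 1 to 4 | Largest difference between periods | True 1500 minus 250 |
|---|---|---|---|
| 0, 0, 0, 0 | 0 | 0 | 0 |
| -300, -200, -100, 0 | -600/4 = -150 | 0 | 300 |
| -1200, -800, -400, 0 | -2400/4 = -600 | 0 | 1200 |
| -2000, 0, 0, 0 | -2000/4 = -500 | 0 | 2000 |

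With an assumed period trend of 0, -50, -100 and -150 ml, period 1 minus period 4 is 150 ml in all four rows, whatever the size effect.

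**Missing data.** Exact cancellation needs complete data. The Discussion section counts 12 of 16 households completing the first period as success. In the second row the 16 values for period 1 sum to 4 × (-600) = -2400. Losing the four households on 1500 ml gives -2400/12 = -200. Losing the four on 250 ml gives (-2400 + 1200)/12 = -100. The mean can therefore lie anywhere from -200 to -100 ml through accidental imbalance. That is still not a contrast between sizes.

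**Reading 2: period means bottle-size condition.** Averaging the same changes by size gives -300, -200, -100 and 0 ml in the second row, and the 1500 minus 250 contrast is 0 - (-300) = 300 ml. It remains 300 ml with the period trend added, because periods are balanced over sizes. For one household with baseline B, (Y_250 - B) - (Y_1500 - B) = Y_250 - Y_1500, so baseline cancels in the difference.

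It does not cancel in a single change. Baseline is a typical weekly amount from till receipts and self-report (Baseline assessments). The intervention outcome is measured from empty, full and partly used bottles (Outcomes and measures). Supply is rounded up to a multiple of 3 l, so 2 l becomes 3 l and 3.5 l becomes 6 l, and it is delivered while other sugary drinks are removed (Intervention). If these together shift every condition by δ, each by-size change is δ + τ_k. It equals τ_k only when δ = 0.

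**Direct analysis.** There are 16 × 4 = 64 household-weeks. A model with household, period and size leaves 64 - 16 - 3 - 3 = 42 residual df. If the residual variance is σ², a within-household difference between two sizes has variance 2σ², so its SD is √2 σ.

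**The case against.** The strongest reply is that a summary by bottle size was intended all along. The Intervention section says the delivered volume is held constant so that it does not differ between intervention periods and confound the bottle-size effect with volume. That makes sense only if a period stands for a size. The abstract likewise treats the week-long interventions as the four sizes, and the planned trial is about bottle size. This stands as a plausible reading, so it cannot be said that the document uses the term for numbered weeks throughout. It does not settle the matter, because Table 1 and the Procedure section define the term the other way.

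Three stronger conclusions might be inferred, and the documents do not support them.

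- *That the summary contains no bottle-size effect at all.* Each period mean contains the average of the four size effects; what is missing is the contrast between them.
- *That a mean change by bottle size could not give the wanted effect.* With complete data, differences between such means are exactly the mean within-household differences between sizes. With dropout, the by-size means come from different sets of households. Subtracting each household's own baseline still removes part of that difference, so pairing is weakened rather than lost.
- *That the main trial will be powered with the wrong SD.* The Data analysis section names no SD, and the choice of variance input can properly be left to a fuller document.

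It is also fair to say that the main analysis is descriptive, that none of the success criteria listed in the Discussion section depends on the effect size, and that consumption is recorded for each household in each week, so the right contrast can always be recovered.

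**Conclusion.** The point holds for the analysis text and not for the design. Under the definition in the Procedure section and Table 1, the stated summary has a between-period contrast of 0 for any bottle-size effect, given complete data, additive effects, no carry-over and no period effect. If period effects exist, the contrast reflects those alone. Followed literally, it does not deliver objective vii. Under the looser reading, the contrast can be had by subtraction, but the quantity actually named, a change from baseline, mixes the size effect with the change of measure and the altered supply. How large that mixing is cannot be judged, since the document gives no figures for it.

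Severity is moderate. Allocation, conduct and data collection are unaffected, and effect size is one of ten objectives. The text still merits correction before analysis, because this figure is intended to set the size of the main trial.

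**What to change.** Replace the effect-size sentence in the Data analysis section with one on these lines: the effect of bottle size will be estimated as the within-household difference in measured weekly volume between sizes (for example each smaller size versus 1500 ml), from a model with household, period and bottle size fitted to all household-weeks. Report each difference with its 95% CI, and the within-household residual SD with its CI (42 residual df with complete data), as inputs for the main trial. Add that under this model the SD of a paired difference is √2 times the residual SD, so that the two are not interchanged in the later calculation. The 1500 ml reference is only an example; the document fixes none.

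Change from baseline can be kept as a description of how consumption during the study compares with usual purchasing, labelled as such. The cost is one sentence of analysis text. No new data, visits or change to the randomisation are needed.

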### Participants

Participating households will be of any size or composition. We define households as people who live together, who may or may not be related but who share all or most drink and food within the house. This includes households consisting ofSingle membersCouples (married or cohabitating)Families with school age childrenSingle parents with dependent childrenFamilies with extended family members living in the house (e.g. grandparents)

In line with the characteristics of the population of SSB consumers in the UK [29], 50 % of the recruited households will be from areas of high deprivation, as defined by their Index of Multiple Deprivation (IMD)^1^ [32] score, with areas falling under the fourth and fifth IMD quintile considered highly deprived. Inclusion criteria for participating households are as follows:i.Purchase regular (not low sugar) Coca-Cola**®** or Pepsi Cola**®** at a minimum rate of 2 l a week.ii.Reside in or near to Cambridge, UK, within 10 miles of the research team base.iii.Do not plan to be away from home for longer than 7 days during the study period.

We will recruit one individual from each eligible household to act as a household representative, who will consent to participation in the study for the entire household and provide all necessary data. In order to evaluate recruitment rates, we will initially approach 100 eligible households with the aim of assessing how many would be interested in taking part in the study and how many would complete the run-in period (see ‘Procedure’ section for details). We assume that households completing this period would be likely to continue, completing at least one intervention period. Of the households completing the run-in period and expressing a willingness to continue with the study, we will invite 16 to continue their participation and undergo the intervention periods. If fewer than 16 households complete the run-in period, we will approach additional households.

Households will be identified and recruited through a research agency.

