The current feasibility and acceptability study is designed to finalise the design and conduct of a future, full-scale trial to assess whether reducing the size of the bottles in which SSBs are presented can reduce consumption. Its primary purpose is to address key design uncertainties for the trial, including the feasibility of recruiting eligible households, the practicalities of delivering the intervention to households and replacing existing SSBs and the feasibility of assessing consumption, as well as the specific bottle sizes that should be targeted. It will be the first study to our knowledge to explore the use a package-size intervention for reducing SSB consumption. Its robust experimental design and naturalistic setting are expected to enhance the value of the findings, whilst inclusion of a qualitative component will also provide a detailed understanding of the acceptability of the intervention. It should be noted,however, that as this is a feasibility study, findings will require replication in larger and more representative samples.

The success of this feasibility and acceptability study will be judged on a number of criteria, including (i) our target sample size is met by approaching 100 households, (ii) recruited households match the deprivation level of typical SSB consumers in the UK (i.e. 50 % are from areas falling under the fourth and fifth IMD quintile), (iii) the majority of participants are not aware of the study’s scientific aim and (iv) at least 12 households out of 16 complete the first intervention period. Should some of these indicators of success not be met, we will consider changes to the study design and procedures before deciding whether and how to proceed with the trial. Specifically, we will consider additional recruitment methods and perhaps widen the target recruitment areas and/or modify the specified eligibility criteria. Larger than expected attrition rates will be accounted for in the trial sample size calculations. Knowledge of the study’s scientific aim could affect the results. Therefore, if we find that most participants are aware of the study aims, we will consider an alternative cover story.

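### The plan powers the main trial on effect sizes observed in 16 households, which are too imprecise for that; a pre-set important difference with the pilot's SD and attrition would serve better.

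*Protocol article*

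**What the plan says.** Data analysis in the protocol article describes one quantitative step beyond descriptive feasibility statistics: "We will also calculate the average change from baseline in SSB consumption during each intervention period". Its stated purpose is "to estimate possible effect sizes from which to power the main trial". Objective vii under Aim and objectives says the same, listing a possible "effect size, to inform sample size calculations for the planned" trial.

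The number of households is set under Participants: "we will invite 16 to continue their participation and undergo the intervention periods". The Sample size section explains that this number does not come from any precision requirement: "Consequently, a formal power calculation is not required", and "The specific sample sizes were selected predominantly based on available resources (i.e. staff and funding"). The success criteria in the Discussion accept that "at least 12 households out of 16 complete the first intervention period".

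The article names no smallest important difference for the main trial and no role for the SD or a confidence limit in sizing it. It does say, in the Discussion, that attrition will enter the main trial's sample size.

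**The concern.** Sixteen households, chosen on resources, are reasonable for judging recruitment, delivery and acceptability. They are not enough to estimate an effect that then sets the size of another trial. The required n varies with the inverse square of the effect, so moderate error in the effect becomes very large error in n. A pilot that overestimates by chance gives a badly underpowered main trial. One that underestimates, or points the wrong way, gives an oversized trial or none. The main trial is meant to inform policy on package size, so either outcome is costly.

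The planned measure adds a second difficulty. Under Intervention and Baseline assessments, baseline is purchased volume from till receipts and self-report, whereas the intervention weeks measure volume consumed. The variability of a change from that baseline is not the variability a crossover comparison of bottle sizes needs.

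**Working it through.** The article gives no main-trial n, so there is no figure to reproduce. The design arithmetic is consistent: 16 households / 4 sizes = 4 per size per period, as in Table 1.

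**Inputs.** From the article: 16 households, 12 as the lowest completion still counted as success (first period only), and a four-period crossover. Assumed, because not stated: two-sided 5%, 80% power, a normally distributed within-household difference, one contrast, no dropout, and a true standardised effect d (mean difference / SD of the difference) from 0.2 to 0.8.

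**Precision of the effect.** Half-width of the 95% CI in SD units = t(0.975, n−1)/√n.
- n = 16: 2.131/4 = 0.53.
- n = 12: 2.201/3.464 = 0.64. A contrast between two sizes needs two completed periods, so it could rest on fewer than 12.

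**Sizing on the observed effect.** Required n = (1.96 + 0.842)²/d² = 7.85/d². Planned n replaces d by the pilot estimate d̂, where 4d̂ follows a noncentral t distribution with 15 df and noncentrality 4d.
- Wrong direction: Φ(−4d); for d = 0.3, Φ(−1.2) = 0.115.
- Planned n within a factor of two of the required n: d/√2 < d̂ < d√2.
- True power of the planned trial = Φ(d√n − 1.96). It is below 50% when d̂ > d × 2.802/1.96 = 1.43d.

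| True d | Required n | Wrong direction | n below half | n within factor of two | n above double, or none | Power under 50% (right-direction pilots) |
|---|---|---|---|---|---|---|
| 0.2 | 197 | 21% | 38% | 22% | 40% | 48% |
| 0.3 | 88 | 12% | 33% | 31% | 36% | 36% |
| 0.4 | 50 | 5% | 28% | 40% | 32% | 29% |
| 0.5 | 32 | 2% | 24% | 48% | 28% | 24% |
| 0.8 | 13 | 0.1% | 17% | 65% | 18% | 16% |

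At d = 0.3, the 10th to 90th centiles of planned n among right-direction pilots are about 17 and 890. With 12 households the within-factor-two share falls to 19% at d = 0.2, 42% at 0.5 and 58% at 0.8.

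**Sizing on a fixed difference with the pilot SD.** Planned n / required n is now χ²(15)/15, whatever d is.
- Within a factor of two: P(7.5 < χ²(15) < 30) = 93%.
- At d = 0.3, the 10th to 90th centiles of planned n are 50 and 130.
- The SD is itself imprecise (95% CI 0.74 to 1.55 times the estimate), and 31% of trials sized this way have under 70% power.
- A one-sided 80% upper limit for the SD is √(15/χ²(0.20; 15)) = 1.21 times the estimate, which cuts that 31% to 8%. Its price is a larger n: 1.206² ≈ 1.46 times. The within-factor-two share becomes P(5.15 < χ²(15) < 20.6) = 84%, with the misses almost all on the large side.
- Using all four periods, the residual has 64 − 1 − 15 − 3 − 3 = 42 df. The factor is then about 1.11 on the SD and 1.109² ≈ 1.23 on n. This assumes equal, uncorrelated residuals, and the SD of a difference is √2 times the residual SD.

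**Which SD.** For one household with baseline B and sizes a and b, (Y_a − B) − (Y_b − B) = Y_a − Y_b. The purchased-volume baseline cancels in a comparison of sizes, so the SD of change from baseline is the wrong input. The right one comes from the same data.

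**The case against.** The wording is hedged: both places speak of possible effect sizes, and neither says the point estimate will be inserted unadjusted. The article is condensed, the main trial will have its own sample size justification, and the Discussion says findings need replication in larger samples. Much of this stands. The simple plug-in rule above is an assumption about how the estimate would be used, and the article's silence on an SD or a target difference is not in itself a fault. But the sentence does name the observed effect as the quantity from which the main trial is powered. The replication caveat limits conclusions about efficacy, not that use.

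The magnitudes rest on an assumed true effect. This also stands. At 0.5 SD planned n misses the factor-two band in 52% of pilots, only just over half, and at 0.8 SD in 35%. It would be wrong to say that the approach usually mis-sizes the trial whatever the true effect.

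A reader might infer that the sizes carried forward under objective iii will be those with the largest observed difference, which would exaggerate the effect further. The article gives no such selection rule; the study's aim is feasibility and acceptability, and the hypothesis is directional. Only if sizes were chosen on observed consumption would the largest of the six contrasts average 2.058/4 = 0.515 residual SD, or 0.515/√2 = 0.36 SD of a difference, with no true effect.

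It is also tempting to say the pilot should supply nothing but the SD. That goes too far: attrition is a proper pilot output, and the Discussion already plans to use it.

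**Conclusion.** The point holds as a recommendation. The plan states that the main trial will be powered on effect sizes from 16 households, and an interval of about ±0.53 SD cannot support that. Under two-sided 5%, 80% power and direct use of the estimate, planned n falls within a factor of two of the required n in about 22% to 48% of pilots for true effects of 0.2 to 0.5 SD. The problem is smaller, though still present, at 0.8 SD. Fixing the difference and taking the SD from the pilot raises the share to 93% at every effect size.

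A reader might conclude that the feasibility study itself is compromised. The article does not support that: recruitment, randomisation, measurement and the four success criteria do not use the effect estimate, and the data needed for the better method will be collected anyway.

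**What to change.** Reword objective vii and the second sentence of Data analysis to say that:

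- the main trial will be powered on a pre-specified smallest important difference in weekly volume consumed;
- the pilot supplies the SD of within-household differences between bottle sizes, not of change from the purchased-volume baseline, and an upper confidence limit is used (for example one-sided 80%: ×1.21 with 15 df, about ×1.11 with 42 df);
- the pilot also supplies attrition;
- observed contrasts between sizes are reported with confidence intervals as descriptive only.

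If observed consumption is to play any part in choosing bottle sizes, the text should say so, because the contrast chosen would then be biased upwards.

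The cost is wording, with no change to the conduct of this study. The main trial's stated n may be somewhat larger: about 23% to 46% above what the unadjusted pilot SD would give, depending on the degrees of freedom used.
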